### Randomization

Enrollment and random allocation will be performed by central registration at the University Hospital Clinical Trial Alliance Clinical Research Supporting System (UHCT ACReSS) at the University of Tokyo. The managers of each site will enroll participants after examining their eligibility and informed consent. The type of allocation will be stratified and block randomization. We will adopt stratification as sites and inpatients/outpatients at enrollment. Owing to allocation concealment, the block size will be provided by UHCT ACReSS and will not be revealed to any researchers or staff until the end of the enrollment period. As this is a single-blinded trial, all assessments after enrollment will be conducted by independent raters with no knowledge of any treatment and care provided this trial.

### Statistical method

All findings will be reported according to the revised CONSORT statement[36]. All analyses will be performed using SPSS 17.0 J (SPSS Inc., Chicago, IL, USA). All data will be analyzed under the intent-to-treat principle. The primary outcome will be analyzed using a simple Student's *t *test and analyzed regarding potential confounders (e.g., age, gender, sociodemographic factors, site, and clinical characteristics) using regression models. Secondary outcomes will be analyzed using relevant tests at each end point and for possible confounders as described for the primary outcome. Subgroup analysis will be conducted at sites and performed for any possible confounders to differentiate the effectiveness of each situation and explore cluster effects.

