## Methods

### Trial design

This trial is designed with effectiveness, interventional, parallel, single-blinded (open but blinded raters) trial. The allocation of participants will be equal (1:1) between the comprehensive approach (CAP) and standard care (SC) groups. The entire trial design is illustrated in Figure 1. After enrollment, all participants will be provided standard care, and in the CAP group, comprehensive community-based care by an early intervention team will be provided for 18 months. Eighteen months after enrollment, all participants will be provided standard care only. The assessment of clinical data will be conducted at enrollment and 18 (first end point), 36 (second end point), and 60 months after enrollment (last end point). The target sample size will be 150, and registration will occur from March 1, 2011, to September 30, 2012. The last follow-up date will be September 30, 2017. This trial was registered in the University Hospital Medical Information Network Clinical Trials Registry (UMIN-CTR) accepted from the International Committee of Medical Journal Editors (ICMJE) (No. UMIN000005092).

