### Outcomes and measurement items

We will adopt the function domain of the global assessment of functioning (GAF-F) [25] scores at the first end point as the primary outcome measure. Secondary outcomes will be GAF-F at the second and last end points, symptom domain of global assessment of functioning (GAF-S), PANSS,[12] the World Health Organization quality of life 26-item version (WHO-QOL26),[26,27] brief evaluation of medication influences and beliefs (BEMIB),[28] care satisfaction of participants and their families, educational and vocational recovery rates, remission rate, re-admission rate, lost to follow-up rate, self-harm and suicide attempt rate, suicide rate, engagement behavior, and direct and indirect costs at each end point. All measurement items will also be assessed at baseline. We will record the presence of comorbid mental and physical disorders and relevant sociodemographic and clinical information about the participants and their families at baseline and at each end point. The details of the assessments are discussed in the following sections.

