### Sample size

The planned number of participants is 150, as determined by previous RCT results, the clustering effects of each site, and the possibility of exhaustion of our resources. An RCT of EIS for patients with FEP in Holland indicated that EIS improved participant GAF-F scores in 24 months[5]. Another RCT of CBT in England revealed that CBT improved patient readmission rates and GAF scores in 18 months[6,7]. The effect sizes calculated from their results were 0.26, 0.46, and 0.58, respectively. The estimated sample sizes using G*Power 3[34] (alpha error = 0.05, beta error = 0.2) were 370, 150, and 96, respectively.

We will adopt 1 interim analysis and consider stopping the trial if the participants in the CAP group have unexpected effective outcomes compared with those in the SC group. We will conduct the interim analysis when half of the participants finish the trials until the first end point. Stopping rules will be planned on the basis of the O'Brien-Fleming method [35] for the GAF-F score, re-admission rate, lost to follow-up rate, self-harm and suicide attempt rate, and suicide rate at the first end point. We will consider stopping the trial on the basis of the stopping rule, baseline data, missing data, and site. Because of ethical issues, we will provide EIS to all participants until 18 months after allocation if the trial is halted.

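### The primary GAF-F analysis leads with an unadjusted t test, which is valid but less precise than a model using baseline GAF-F and the stratification factors

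*Protocol article*

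**What the plan says.** All places are in the Methods of the protocol article.

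- **Outcomes and measurement items** takes GAF-F "scores at the first end point as the primary outcome measure". The first end point is 18 months. The same section states: "All measurement items will also be assessed at baseline". Baseline GAF-F is therefore collected.
- **Randomization** uses stratified blocks: "We will adopt stratification as sites and inpatients/outpatients at enrollment". There are four sites.
- **Statistical method** says: "The primary outcome will be analyzed using a simple Student's" t test. The sentence continues that the outcome will also be "analyzed regarding potential confounders (e.g., age, gender, sociodemographic factors, site, and clinical characteristics) using regression models".

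Site, one of the two stratification factors, is among the examples in that clause. Inpatient/outpatient status and baseline GAF-F are not named, although the phrase about clinical characteristics could cover them. The section does not say whether the t test or the regression decides the trial's primary result.

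**The concern.** Stratified block randomisation balances the arms within site and within inpatient/outpatient status. To the extent that these factors predict GAF-F, the arm difference varies less from one randomisation to the next than it would under simple allocation. An unadjusted t test does not register this: its standard error still contains the between-stratum variation. Its intervals are then too wide and its type I error falls below the nominal level.

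Baseline GAF-F raises a separate matter. If it correlates with the 18-month score, adjusting for it removes that share of the residual variance, and the t test forgoes the gain.

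What is at stake is precision in a trial of 150 with little to spare. It also matters which analysis counts as primary if the adjusted and unadjusted results fall on different sides of 0.05.

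**Working it through.** **Inputs from the document.** The total is 150 (Sample size: "The planned number of participants is 150, as determined by previous RCT results, the clustering effects of each site"). Allocation is 1:1 (Trial design: "The allocation of participants will be equal (1:1) between the comprehensive approach (CAP) and standard care (SC) groups"), so 75 per arm. The error rates are "alpha error = 0.05, beta error = 0.2". Taken in the order of the text, the effect sizes are 0.26 (GAF-F in the earlier trial of early intervention services), 0.46 (readmission) and 0.58 (GAF), with stated totals of 370, 150 and 96. Sidedness is not stated.

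**Inputs assumed.** The correlation r between baseline and 18-month GAF-F is taken as 0.3 to 0.6. The share of outcome variance explained by the strata, R², is taken as 5 to 10%. Follow-up is taken as complete.

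**Step 1: reproduce the planned size.** For two means, n per arm = 2(1.96 + 0.8416)²/d². At d = 0.46 this is 15.70/0.2116 = 74.2, rounded up to 75, a total of 150, as stated. The exact noncentral t calculation gives 152, which agrees within the rounding of d. At d = 0.58 the two methods give 94 and 96, against 96 stated. Two-sided testing is therefore used below. (At d = 0.26, two-sided testing gives 466 or 468, not 370; one-sided testing gives 366 or 368. That is a separate point, and nothing below depends on it.)

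**Step 2: power of the plain t test.** With 75 per arm the noncentrality is d√(75/2) = 6.124d. Exact two-sided power is 79.9% at d = 0.46 and 35.3% at d = 0.26.

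**Step 3: adjust for baseline GAF-F.** The residual SD becomes SD × √(1 − r²), so d is replaced by d/√(1 − r²). The equivalent unadjusted trial size is 150/(1 − r²). The few degrees of freedom used by covariates are ignored.

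| r (assumed) | SE relative to t test | Equivalent unadjusted N | Power, d = 0.46 | Power, d = 0.26 |
|---|---|---|---|---|
| 0 (t test) | 1.00 | 150 | 79.9% | 35.3% |
| 0.3 | 0.95 | 165 | 83.5% | 38.2% |
| 0.4 | 0.92 | 179 | 86.3% | 40.8% |
| 0.5 | 0.87 | 200 | 89.8% | 44.7% |
| 0.6 | 0.80 | 234 | 93.8% | 50.7% |

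Beyond the assumed range, r = 0.7 gives 60.1% at d = 0.26, still well below 80%.

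**Step 4: effect of ignoring the strata.** With arms balanced within strata, the true standard error is √(1 − R²) times the one the t test uses. The true type I error is then 2[1 − Φ(1.96/√(1 − R²))].

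- R² = 0.05: 1.96/0.9747 = 2.011, giving 4.4%.
- R² = 0.10: 1.96/0.9487 = 2.066, giving 3.9%.

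The power cost of omitting the strata alone is small. At d = 0.46, power is 80.6% unadjusted against 81.9% adjusted when R² = 0.05, and 81.2% against 83.9% when R² = 0.10. Most of any gain would come from baseline GAF-F.

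**The case against.** The strongest reply is that the plan already adjusts. The sentence that names the t test also plans regression on the primary outcome, and it lists site and clinical characteristics. A reader might infer that the plan ignores the stratification factors altogether. That is true of the t test but not of the plan as a whole.

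A reader might also infer that the open list of covariates lets the model be chosen after the data are seen. The document does not support this. It is a journal article, and the exact covariates may well be fixed in a statistical analysis plan that is not shown.

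Nor is the t test invalid. Its error rate is below 5%, not above it. Chance baseline imbalance in a randomised trial is random error that the t test's standard error already covers, not bias. The test also matches the two-group calculation behind the planned 150.

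Finally, the size of the gain rests on a correlation the document does not give. At r = 0.3 the gain is under four percentage points at d = 0.46.

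All of this stands, and it lowers the weight of the point. What it leaves is that the article itself names the unadjusted test first and puts an adjusted analysis beside it without ranking the two. A later analysis plan can add covariates, but promoting an adjusted model over the published t test would be a visible change of primary analysis, so it is better made early.

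**Conclusion.** The point holds as a recommended improvement, not as a defect that must be fixed before the trial can be interpreted. The lead analysis is valid, mildly conservative and less efficient than the design and the baseline data allow.

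Under the stated assumptions, adjustment would add roughly 4 to 14 percentage points of power at d = 0.46 and 3 to 15 at d = 0.26. If r is below 0.3 the gain is smaller. Loss to follow-up would lower all the power figures.

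It would be wrong to conclude that adjustment solves the trial's power problem. At d = 0.26, the effect the article derives for GAF-F itself, the article states a need for 370 participants against 150 planned. Power there reaches only about half even at r = 0.6. That shortfall is a matter of sample size, not of the choice of test.

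**What to change.** Before the planned interim analysis, and in any case before unblinding, name as the primary analysis a linear model of 18-month GAF-F on arm, baseline GAF-F, site (four levels) and inpatient/outpatient status at enrolment. Report the adjusted mean difference with its 95% confidence interval. Keep the Student's t test as a supportive analysis and label any further confounder regressions exploratory. Since GAF-F is also part of the interim stopping rule, say that the same model applies there.

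The cost is a sentence or two in the Statistical method section. The article already provides for collecting every variable, the sample size does not change, and the model is a standard one for the named software. The statistical price is five degrees of freedom (one for baseline GAF-F, three for site, one for inpatient/outpatient status), which is negligible with 150 participants.

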## Discussion

This trial has some possible limitations regarding sample size and the duration of case management. Previous studies of EIS for patients with FEP have suggested that although 1.5-year EIS improved patient social functions and readmission rates, these effects did not persist (5 years)[23,24]. However, these results also depend on the treatment provided to the control group, and community mental health services are widely available in Holland and England[1]. In the present situation in Japan, little psychological education is provided in schools and the workplace, and few mental health services are available in the community setting; consequently, much prejudice, discrimination, and stigma exists regarding psychosis[10]. In addition, we will emphasize "graduating from the service" in that case managers will continue to provide services after EIS after a participant enrolls in the trial. Therefore, this trial will demonstrate the effectiveness of EIS in Japan and also explore and consider exit strategies for EIS. Finally, the results of this trial will be used to inform policy makers and practitioners about the benefits, required human resources, and cost-effectiveness of EIS. This trial will provide helpful results about the effectiveness and cost-effectiveness of EIS in Japan to improve the quality and quantity of community mental services.
